## Abstract

Enhanced neuronal synchronization of the subthalamic nucleus (STN) is commonly found in PD patients and corresponds to decreased motor ability. Coordinated reset (CR) was developed to decouple synchronized states causing long lasting desynchronization of neural networks. Vibrotactile CR stimulation (vCR) was developed as non-invasive therapeutic that delivers gentle vibrations to the fingertips. A previous study has shown that vCR can desynchronize abnormal brain rhythms within the sensorimotor cortex of PD patients, corresponding to sustained motor relief after 3 months of daily treatment. To further develop vCR, we created a protocol that has two phases. Study 1, a double blinded randomized sham-controlled study, is designed to address motor and non-motor symptoms, sensorimotor integration, and potential calibration methods. Study 2 examines dosing effects of vCR using a remote study design. In Study 1, we will perform a 7-month double-blind sham-controlled study including 30 PD patients randomly placed into an active vCR or inactive (sham) vCR condition. Patients will receive stimulation for 4 h a day in 2-h blocks for 6 months followed by a 1-month pause in stimulation to assess long lasting effects. Our primary outcome measure is the Movement Disorders Society-Unified Parkinson's Disease Rating Scale (MDS-UPDRS) part III off medication after 6 months of treatment. Secondary measures include a freezing of gait (FOG) questionnaire, objective motor evaluations, sensorimotor electroencephalography (EEG) results, a vibratory temporal discrimination task (VTDT), non-motor symptom evaluations/tests such as sleep, smell, speech, quality of life measurements and Levodopa Equivalent Daily Dose (LEDD). Patients will be evaluated at baseline, 3, 6, and 7 months. In the second, unblinded study phase (Study 2), all patients will be given the option to receive active vCR stimulation at a reduced dose for an additional 6 months remotely. The remote MDS-UPDRS part III off medication will be our primary outcome measure. Secondary measures include sleep, quality of life, objective motor evaluations, FOG and LEDD. Patients will be evaluated in the same time periods as the first study. Results from this study will provide clinical efficacy of vCR and help validate our investigational vibrotactile device for the purpose of obtaining FDA clearance.

**Clinical Trial Registration:**
ClinicalTrials.gov, identifier: NCT04877015.

## Introduction

More than 6.1 million people suffer from Parkinson's Disease (PD) worldwide (1), making it the most widespread neurodegenerative disorder second to Alzheimer's Disease (2). Dopamine precursors, such as levodopa, are used in medication to treat PD and are considered the gold standard in improving motor function (3). However, given that PD is a neurodegenerative disease resulting in patients' symptoms worsening over time, dopaminergic therapy can only go so far before patients increase their medication or no longer feel the same therapeutic benefit (3, 4). Furthermore, medications that increase dopaminergic transmission can have unwanted side effects, such as vomiting, hypotension, delusions, and dyskinesia (5). In addition, dopaminergic induced psychosis is often reported in PD patients, especially those in the advanced stages of the disease who experience cognitive impairment (6). In the later stages of PD, patients may undergo Deep Brain Stimulation (DBS), which has demonstrated to be more effective than medication alone (7). However, the invasiveness of the procedure and related potential surgical side effects (e.g., hemorrhage) (8) as well as side effects of the chronic stimulation, considered as DBS-induced movement disorders (9), make it less appealing to patients. For instance, different types of dyskinesias, blepharospasm, and apraxia of eyelid opening were observed with DBS delivered to the subthalamic nucleus (STN), whereas hypokinesia and freezing of gait were described with DBS of the globus pallidus internus (GPi) (9). Furthermore, DBS delivered to standard targets for PD, such as the STN or GPi, is less effective in treating gait, balance (10), and dysarthrophonia (11). Even in conjunction with medication, traditional high frequency DBS only provides temporary motor improvement, with symptoms returning almost immediately after cessation of stimulation (12). The development of non-invasive therapies that improve PD symptoms and potentially change pathological PD brain states in a way which slows, or reverses disease progression is much needed and essential in overcoming the limitations of the two most common types of PD treatments (13).

Abnormal neuronal synchrony of beta band is often found within the STN of PD patients (14), with decreases in this band correlating with improved motor capability (15). Based on this finding, we developed vibrotactile Coordinated Reset (vCR) which is a non-invasive treatment that delivers weak, non-painful random vibrations to the fingertips of patients (16). This type of therapy is based on extensive computational research done on the desynchronizing effects produced by CR (17–19). CR stimulation aims at disrupting neuronal synchronization by delivering phase resetting stimuli, typically periodically in time, separated by equidistant time differences given by T_s_/N_s_, where T_s_ is the duration of a stimulation cycle, and N_s_ is the number of active stimulation sites (20). Computationally, it was shown that CR-induced desynchronization may cause a reduction of the rate of neuronal coincidences, and in turn, a decrease of the strength of plastic synapses, ultimately shifting neural networks from stable, synchronized, strongly synaptically-connected states to stable desynchronized states with weak connectivity (18–21). For this, CR uses spike-timing-dependent plasticity (STDP), a fundamental learning mechanism that adapts the strength of synapses based on the relative timing of their pre- and postsynaptic spikes or bursts (22). Furthermore, in this study, we consider a vCR pattern with moderate stimulus time jitter. This is motivated by a previous computational study introducing spatial and temporal jitter (21). To this end, random reset (RR) stimulation was administered to a network of leaky integrate-and-fire (LIF) neurons with STDP and electrical model stimuli (21). It was shown that RR stimulation, characterized by adding spatial and temporal noise to the mechanism of CR stimulation, may lead to more robust long-term desynchronizing effects, that are less dependent on the detuning of the mean inter-stimulus interval in comparison with the dominant frequency of the abnormally synchronized neuronal rhythm (21).

In a previous study, monkeys injected with 1-methyl-4-phenyl-1,2,3,6-tetrahydropyridine (MPTP) received brief, high frequency electrical pulse trains that were administered to the STN (CR-DBS) for 2 h on five consecutive days (23). Acute and sustained motor improvement lasting for several weeks was observed (23). This study was then performed with PD patients who received CR-DBS administered to the STN for 4 h a day for three consecutive days. Reduced beta band synchronization occurred, which correlated with a significant improvement of motor ability (24).

Taken together, we believe that vCR has the potential to drastically improve motor abilities during and post treatment, decrease patient medication intake and potentially slow disease progression in a way that is non-invasive and presents little to no side effects. The current study protocol: *Vibrotactile coordinated reset: a non-invasive treatment for Parkinson's disease*, aims to understand the therapeutic benefits of vCR in a larger sample size, test against a dedicated sham pattern, study vCR effects on not only motor outcomes, but voice, speech, sleep and other non-motor symptoms, study vCRs long-lasting effects, and finally a vCR dosing regimen all within a 14-month clinical study protocol. Together, results from this study will demonstrate clinical efficacy of our vCR stimulation pattern and vibrotactile device for the purpose of acquiring Food and Drug administration (FDA) clearance.

## Methods and Analysis

### Vibrotactile Coordinated Reset Therapy

Noisy vCR stimulation (see Figure 1 for a schematic representation) was introduced by Pfeifer et al. (17). Vibratory stimuli are delivered at periodic times with a jitter that is uniformly distributed within the range of ±23.5% the inter-stimulus intervals. A vCR cycle comprises a sequence of four vibratory bursts delivered to each fingertip. The vCR sequence is randomly varied from one cycle to another. Three cycles with vCR stimulation ON are followed by two cycles with vCR turned OFF (3:2 ON–OFF CR). We apply bilateral noisy vCR in a mirrored manner, such that the right and left fingers two to five get coincidently activated, respectively. Vibration frequency is 250 Hz and duration of vibration bursts amounts to 100 ms. As in Pfeifer et al. (17) the CR frequency (*f*_*CR*_), which is the CR sequence delivery rate, is 1.5 Hz. Accordingly, the length of a CR cycle is 667 ms. The duration of a single vCR session amounts to 2 h. To avoid patient unblinding, the parameters for the sham stimulation will be presented in our clinical results paper upon completion of this study.

**Figure 1 F1:**
[figure not shown]
Schematic illustration of the vCR stimulation using a three cycles ON: two cycles OFF pattern (17). Single vibratory bursts (highlighted by red bars) are delivered at periodic times subjected to a jitter that is uniformly distributed within the range of ±23.5% the inter-stimulus intervals. A vCR sequence comprises four subsequent vibratory bursts, delivered (on average) within one vCR cycle. Within one vCR sequence each fingertip (two through five) is activated exactly once. The CR frequency *f*_*CR*_, i.e., the rate at which the CR sequences are delivered, is 1.5 Hz. Hence, the length of a CR cycle is 667 ms. Bilateral noisy vCR is administered in a mirrored manner to both hands, coincidently activating right and left fingers (two through five). Schematic shows the vCR pattern coincidently delivered to left and right hand. Vibration frequency is 250 Hz and duration of vibration bursts is 100 ms. The duration of a single vCR session is 2 h.

### Vibrotactile Device Description

The vibrotactile device is investigational and has not yet been cleared by the FDA for clinical use. The vibrotactile device is a mobile, battery-operated controller with wire-connected vibrotactile stimulators (tactors) fastened onto the fingertips of a custom glove (see Figure 2). The glove is fitted by trained clinical research coordinators during the baseline visit. Both sham and active vCR stimulation patterns were developed by the study's principal investigator and were tested together with Engineering Acoustic Incorporated (EAI). Stimulus patterns are loaded into the controller *via* secure digital (SD) cards. The controller is small enough to fit into a pocket or can be fastened to a belt (Figure 2B). The tactors (Figures 2A,B) are connected to a glove and are individually fastened to the fingertips *via* elastic Velcro bands. The tactors are connected to the controller (Figure 2C) and an Organic Light-Emitting Diode (OLED) screen displays information about battery status and the time left in the therapy session. The controller has a push button that can start, pause or turn off the device (Figure 2D). The controller logs patient therapy sessions and stores this information on the SD card. The research personnel uses the log information to verify that each patient is stimulating according to the stimulation protocol procedures. The controller has a charging port on its side (Figure 2E) and is charged with a micro-USB.

**Figure 2 F2:**
[figure not shown]
Displays the vibrotactile wearable stimulator. **(A)** Displays the tactors and gloves that can be adjusted *via* Velcro straps for the finger pad or length of finger. **(B)** Depicts the controller being worn and fastened by a belt. **(C)** Displays the part of the controller in which the tactor ends plug into. **(D)** Displays the LCD screen which shows battery life and time remaining of stimulation. A push button turns on, pauses, and turns off the controller. **(E)** Displays the charging port of the controller which is charged with a micro-USB.

### Patient Population

Patients will be screened and selected from the population of patients presenting with idiopathic PD who are routinely seen in the Stanford Neuroscience Clinic, referred from non-Stanford clinics or have found this study through clinicaltrials.gov. The principal investigator, designated movement disorders neurologist and research coordinators may introduce the study to potential candidates in-person at Stanford's Neuroscience Clinic. Additionally, clinical research coordinators may also contact potential candidates by phone or email after the referral. Patients allowed into the study will only be from the San Francisco Bay area.

### Inclusion and Exclusion Criteria

Patients included in this trial will be between 45 and 85 years of age and have a diagnosis of idiopathic Parkinson's disease with Hoehn and Yahr Stages II–IV while on medication. Patients will need MDS-UPDRS III motor improvement ≥30% while on medication compared to while off medication and be on stabilized medication. Patients cannot have dopamine dysregulation syndrome or presence of other neurological diseases such as major depression, dementia, attention deficit disorder, psychosis, or essential tremor. Patients cannot have a history of epilepsy, traumatic brain injury or brain surgery. Patients cannot have severe sensory abnormalities of the fingertips such as vibratory urticaria. Patients must clearly communicate with staff and speak English. Patients are excluded if they are currently on psychoactive or narcoleptic medications or are on medications that affect brain function or alter EEG recorded activity (i.e., anticonvulsants, ADHD, depression, or anxiety medication). Participation in this study requires that all patients do not participate in another drug, device, biologic, or intervention trial concurrently or within the preceding 30 days. Patients who are pregnant, breastfeeding, or trying to get pregnant during the duration of the study are excluded. Lastly, San Francisco Bay area residents may only be included in this study.

### Pre-assessment Measures for Inclusion of Clinical Trial

Prior to on-site assessment measures, patients will receive a General Health Survey which includes questions regarding health history, inclusion/exclusion criteria and questions relating to dopamine dysregulation syndrome. If the patient is considered a good candidate, a trained staff neurologist, specialized in movement disorders, will verify idiopathic PD in potential patients at an on-site pre-study visit, four-eight weeks before the initial trial. Depending on the type(s) of Parkinson's medication the patient takes, he or she will be asked to withdraw from medication (12–48 h) prior to the in-person assessments. On-site, patients will be asked about their health history and a series of neurological and physical examinations will be performed by the study's movement disorders neurologist to rule out patients with physical or neurological problems unrelated to PD that may impact the study results. Verification of motor responsiveness to dopaminergic medication will be assessed using part III (motor evaluation) of the MDS-UPDRS. Patients will arrive off medication and perform the MDS-UPDRS III. Patients will then be prescribed Parcopa, a carbidopa-levodopa orally disintegrating, fast acting tablet that takes ~1 h to take effect after which the MDS-UPDRS III will be performed again. Patients will then additionally perform the Mini Mental State Examination (MMSE) (30) and Scales for Outcomes in Parkinson's disease-Cognition (SCOPA-COG) (31) to rule out PD dementia. To exclude patients with severe vibratory sensory abnormalities, such as vibratory urticaria, patients will receive vibrations with high (0.35 mm) and low (0.03 mm) peak vibration amplitudes to each individual fingertip and be asked to verify which vibration type they received. Each patient's medication is then tracked for 1 month by the movement disorders neurologist to confirm that the patient's medication is stable.

### Study Personnel and Their Roles

This study will include five movement disorders neurologists who are blinded during the first study. The first movement disorders specialist will serve as the *treating movement disorders neurologist* and perform physical and neurological examinations, evaluate and provide medical advice regarding patients' medication intake and serve as point of contact in the event of a serious or adverse event either unrelated or related to vCR for both the first and second study. The second movement disorders neurologist will serve as the studies' *main MDS-UPDRS movement disorders evaluator* who will perform assessments on patients throughout the first and second study. Three other movement disorders specialists will serve as the study's *video MDS-UPDRS III raters* for the first (main) study. The clinical research coordinators will oversee consent, objective motor measurements, video recordings, patient contact, vibrotactile glove administration, EEG recordings, voice recordings, and all self-report tests and questionnaires in both studies. Speech analysis will be performed by a voice disorders specialist and her trained team. An un-blinded statistical analyst, who is not associated with the study team and does not report to any member of the study team, will perform all statistical tests on outcome measures. All movement disorders specialists, speech analysis, and clinical research coordinators, will be blinded until completion of the first study.

### Study 1 Design: Main Phase—Double Blind Sham-Controlled

We will perform a 7-month, double-blind, sham-controlled study including 30 PD patients randomly placed into either active vCR (*n* = 15) or a sham (*n* = 15) condition. All personnel and PD patients will be completely blinded to which stimulation pattern patients obtain. Parkinson's patients will receive vCR or sham stimulation for a total of 4 h a day (2 times 2 h a day with a break in between the 2-h sessions) at home for 6 months. To measure long-term effects, patients will pause stimulation for 1 month after the 6-month follow-up appointment.

#### Assessments: Study 1

The following outcome measures and their descriptions will be administered to patients. The *MDS-UPDRS parts IA, IB, II, III*, and *IV* (29). The MDS-UPDRS parts IA and IB concerns non-motor experiences of daily living, in which IA is assessed by the study's main MDS-UPDRS movement disorders evaluator and IB is self-reported. Part II is motor experiences of daily living and is self-reported. Part III is the in-person motor evaluation assessed by the study's main MDS-UPDRS movement disorders evaluator. In addition, part III will be video recorded and sent to the three blinded video MDS-UPDRS III raters. Patient recordings will be evaluated after each patient completes his or her 7-month visit. Video raters will additionally be blinded to the date of administration. Part IV incorporates patient details on motor complications with the study's main MDS-UPDRS movement disorders evaluators observations and judgements. The *PD Quality of Life Questionnaire-39* (*PDQ-39*) (32) is a self-report questionnaire that examines health related difficulties specific to PD in eight quality of life categories within the last month. The *Parkinson's disease sleep scale* (*PDSS-2*) (33) examines PD related sleep issues during the past week. The *University of Pennsylvania Smell Identification Test* (*UPSIT*) (34) is a smell test comprised of 40 odors, in which patients try to correctly identify the odorant presented. Patients will also take a tolerability and usability questionnaire regarding the vCR device. We will perform a *vibratory temporal discrimination task* (*VTDT*) that consists of two vibratory bursts, with one burst delivered to the index finger and one burst to the middle finger. Each burst will start randomly on either the index or middle finger. This procedure will be performed on the right and left hand separately. The patient is instructed to judge if he/she felt a delay between the two vibratory bursts. This task was designed as a possible calibration method for future vCR studies by serving as a sensitivity measure for vibratory temporal changes, in which reduced perceived vibratory time differences correspond to increased vibratory temporal discrimination. Patients will also undergo clinically established *speech and voice assessments*. Speech samples will be collected at a sampling rate of 44,100 Hz on a laptop using the Praat Speech Analysis program (Version 5.4, University of Amsterdam). To collect samples, a head-worn, unidirectional microphone will be placed over the participant's ears and the microphone will be adjusted so that it is 6 cm from the participant's mouth. Specific samples will include sustained vowel phonations, sentence and paragraph length reading passages, and spontaneous speech. From these samples, speech and voice assessments will be conducted including measures of articulatory precision, speech intelligibility, speech rate, auditory-perceptual ratings of voice, and acoustic measures of vocal fundamental frequency, vocal intensity, and fundamental frequency and intensity variability. Additionally, the sentence intelligibility portion of the Assessment of Intelligibility in Dysarthric Speech (AIDS) (35) and patient self-assessment scales of Communicative Participation Item Bank (CPIB) (36) and the voice handicap index (VHI) (37) will be collected. For objective measures, patients will perform the *Kinesia ONE* motor evaluation, which uses a wearable accelerometer to assess motor activities similar to the MDS-UPDRS III and record their Parkinson's medication intake. The *Ambulatory Parkinson's Disease Monitoring* (*APDM*)'s Mobility Lab system will be used to measure objective gait disturbances. Lastly, the patient will also complete three different types of tasks during which *EEG* will be recorded. The first is a *sensorimotor EEG task*, in which patients receive a single vibratory stimulus to a random finger (excluding the thumb) on their non-dominant hand and are instructed with their dominant hand to push the response pad as fast as possible when they feel the vibratory burst. Each finger receives an equal number of vibratory pulses (50 per finger, equaling 200 trials) in a randomized order. Cortically, we expect to look at motor evoked potentials in response to cued vibration and their amplitude and latency changes throughout the course of treatment. Reaction time will also be documented. Additionally, we will record *vibration-only evoked potentials* in which we look at how two different types of vibratory pulses (high- and low- amplitude) affect different motor and sensory areas of the brain. The last task will be a recording done while the patient is at rest (*spontaneous EEG*). Patients will receive either active vCR or sham depending on the condition to which they were randomly assigned. For this task, we want to replicate our previous finding of decreased high beta band power (21–30 Hz) (17) for patients who received real vCR and quantify differences in activated brain areas in response to sham or active vCR. The MDS-UPDRS III off medication will be used as our primary outcome measure. All other measures are considered secondary.

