#### Study 1: Statistical Analysis and Anticipated Results

A sample size of 30 was selected as a starting number of patients for the clinical trial. A priori analysis indicated that for a sample size of 30, we would need a large effect size (*f* = 0.42) in order to reach statistical significance (*p* ≤ 0.05). In our previous study of six patients receiving vCR treatment for 3 months, using a paired samples *t*-test to compare MDS-UPDRS III scores pre- and post-treatment, the effect size was large (*d* = 1.011) (17). Based on this, our large *f* effect size of 0.42 may be reasonable. Nevertheless, an interim analysis will be performed by an un-blinded, experienced statistical research personnel, who is unaffiliated with the study team and does not report to any study team member, the principal investigator, nor any neurologist involved in the studies. This interim analysis will be performed when 16 patients have completed the 3-month mark, with eight belonging to the sham group and eight belonging to the vCR group. Results from the interim mixed factorial analysis of variance (ANOVA), will allow us to recalculate our desired sample size.

A 2 (sham vs. real vCR) by 4 (baseline, 3, 6, and 7 months) mixed factorial ANOVA will be done separately on the following measures: MDS-UPDRS I, II, III, IV, Levodopa equivalent daily dose (LEDD), EEG sensorimotor related evoked components, vCR resting EEG beta power response, vibratory temporal discrimination, speech assessments, UPSIT, PDSS, PDQ-39, FOG, and gait measurements obtained from the APDM Mobility Lab.

Statistically, for patients who received real vCR, we hope to see significant improvement in all measures by 6 months and expect to see no significant worsening when comparing assessments done after the pre-planned 1-month pause in stimulation at 7 months. In addition, we expect to see no significant improvements in the sham group patients.

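### The primary endpoint is at 6 months, but the only named analysis is a four-visit ANOVA that, run conventionally, drops a patient who misses the post-pause 7-month visit

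*Protocol article*

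**What the plan says.** The Abstract places the primary outcome at one time point: MDS-UPDRS "part III off medication after 6 months of treatment". The Study 1 assessments section repeats the measure without the time point: "The MDS-UPDRS III off medication will be used as our primary outcome measure".

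Study 1 visits are at baseline, 3, 6 and 7 months. The last follows a month without stimulation and is meant to show whether effects persist.

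The Study 1 statistical section names one method for part III and for nearly all other measures: "A 2 (sham vs. real vCR) by 4 (baseline, 3, 6, and 7 months) mixed factorial ANOVA". It gives no separate 6-month comparison for part III.

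On who scores part III, the assessments section says: "Part III is the in-person motor evaluation assessed by the study's main MDS-UPDRS movement disorders evaluator". It then adds a second set of ratings: "In addition, part III will be video recorded and sent to the three blinded video MDS-UPDRS III raters". Their timing and masking are given next: "Patient recordings will be evaluated after each patient completes his or her 7-month visit", and "Video raters will additionally be blinded to the date of administration".

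**The concern.** The endpoint is at month 6, but the named analysis also runs over month 7. A classical mixed factorial ANOVA with a four-level visit factor uses only patients with a score at every level. Whether a 6-month score counts then depends on attending a later visit that is not part of the endpoint. Patients who leave before month 6 have no 6-month score, but the same method also discards their baseline and any 3-month scores, which carry information about the group comparison.

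With 15 patients per arm, each lost patient costs precision. If the reasons for leaving relate to outcome and differ by arm, an analysis of completers can also be biased. A model that uses the available visits would avoid losing the recorded 6-month scores at almost no cost.

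**Working it through.** **1. Endpoint and method side by side.**
- Endpoint (Abstract): part III off medication, month 6.
- Method (Study 1 statistical section): visit factor with levels baseline, 3, 6 and 7 months.
- Conventional requirement: four scores per patient.

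| Visits attended | 6-month score recorded? | In a conventional 2 × 4 ANOVA? | What is discarded |
|---|---|---|---|
| 0, 3, 6, 7 | yes | yes | nothing |
| 0, 3, 6 | yes | no | baseline, 3- and 6-month scores |
| 0, 3 | no | no | baseline and 3-month scores |
| 0 only | no | no | baseline score |

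Only the second row loses a recorded endpoint value, and it covers the single month of the pause.

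**2. The plan's own figure.** The article gives N = 30 and f = 0.42 at a 0.05 level, without power or within-patient correlation. Assume a correlation ρ = 0.5 and take the between-group test of the 2 × 4 design (m = 4 visits):

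λ = f² · N · m / (1 + (m − 1)ρ) = 0.1764 × 30 × 4 / 2.5 = 8.47, with 1 and 28 degrees of freedom.

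The noncentral F distribution gives power 0.802, and 30 is the smallest even N that reaches 80%. The stated pair is thus reproduced as about 80% power, with all 30 patients contributing all four visits.

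**3. Cost of complete-case loss (assumed rates).** The article states no dropout rate, so 10% and 20% serve as a range.
- Standard error: √(30/27) = 1.054, about 5% wider; √(30/24) = 1.118, about 12% wider.
- Power of the test in step 2 at ρ = 0.5: 0.756 with 27 patients and 0.701 with 24.
- Sensitivity to ρ, from 30 to 24 patients: 0.896 to 0.814 at ρ = 0.3, and 0.713 to 0.608 at ρ = 0.7.

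These figures treat all incomplete patients alike. A model on available visits fully recovers the 6-month score of someone who misses only month 7. For earlier leavers it recovers only what their earlier visits tell about month 6.

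**4. Possible bias (hypothetical).** Suppose 3 of 15 patients in one arm attend month 6 but not month 7, and their 6-month scores average 6 points worse than the rest. Dropping them makes that arm's mean look 3/15 × 6 = 1.2 points better than it is. Neither input comes from the article, and the sum applies only to patients lost in that one-month window.

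**5. Video ratings.** The timing sentence ties rating to completion of the 7-month visit. Taken literally, recordings of a patient without that visit never fall due. The in-person score is made at the visit itself and is unaffected.

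**The case against.** The strongest reply is that the article contains no rule limiting the analysis to completers. It states no analysis set and no missing-data method, and a statistical analysis plan that is not shown may supply both. That stands as far as missing-data rules go, and their absence is not the point here. The point is the method the article does fix: used as named, it has this consequence, and it does not isolate the 6-month comparison.

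A second reply is that the window is narrow and the mechanism weak. No one is stimulating between months 6 and 7, so the burden of 4 h a day cannot drive absence then. The 7-month appointment is also where patients are unblinded and offered active treatment, which is a reason to attend. This stands, and it limits how many recorded 6-month scores could be lost.

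A third reply is that an interim ANOVA is planned when 16 patients reach month 3, so analysis without 7-month data is foreseen. However, that analysis serves sample-size recalculation and does not change the final one.

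On the videos, a reader might infer that leaving before month 7 forfeits the primary endpoint because the recordings are never rated. The document does not support this. The sentence sets timing, which fits the date masking beside it, and states no exclusion. The video ratings are additional to the in-person score of an evaluator who is also blinded in Study 1, and nothing makes the video score primary. Standard operating procedures, which the article says exist for all evaluations, may cover early leavers.

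**Conclusion.** The point holds for the analysis method. A 6-month endpoint is analysed only through a four-visit ANOVA that conventionally drops anyone who misses a visit, including one after the endpoint. A better-suited method is readily available, so the change should be made.

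The size cannot be fixed from the article. On assumed losses of 3 or 6 of 30 patients, the standard error widens by about 5% or 12%. Power for the between-group test falls from 0.802 to 0.756 or 0.701 if the within-patient correlation is 0.5. Loss of recorded 6-month scores is confined to the pause month, and the 1.2-point bias is an illustration, not an estimate.

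Two stronger readings should not be drawn: that the plan makes the 7-month visit a written condition of entry to the analysis, and that early leavers lose a 6-month score already made in person. The video sentence needs only a clarification.

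**What to change.** In the Study 1 statistical section, replace the 2 × 4 mixed factorial ANOVA for the primary outcome with a likelihood-based repeated-measures mixed model. It should have terms for group, visit and group-by-visit, use small-sample degrees of freedom, and include all available visits of every randomised patient. Name the group difference at 6 months as the primary contrast. A missing month 7 then cannot remove a month-6 score.

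As a secondary clarification in the Study 1 assessments section, say that recordings are rated after the 7-month visit or study exit, whichever comes first. Date masking can be kept.

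The cost is about two sentences, a few more ratings by the same three raters, and no new visits. The model relies on a missing-at-random assumption and on a covariance structure that must be chosen in advance. Both are modest prices in a trial of this size.
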